##### Sample Size

For cluster randomization, sample size calculations were based on sample size requirements developed by Heo and Leon [35] to detect the intervention by time interactions in longitudinal cluster randomized clinical trials. This trial is powered to detect differences in the overall student sample across three time-points. Five schools, with an average of 70 students per school, are required per intervention group; this would achieve an 80% power to detect a standardized, between-group mean difference of 0.2 (*P*=.05) in primary outcomes at the end of the trial, with 3 measurement occasions. An effect size of 0.2 is comparable with previous trials of combined student and parent programs (effect size range: 0.2-0.3) [36]. To account for school dropouts during the trial, which we expect to be approximately 15%, we aim to recruit at least 12 schools in total. Assuming that the majority (if not all) students in the year group participate in this study (approximately 70 on average; based on participation rates found in previous school-based trials of a similar nature [18-21,23,24,37]), it will give us a total of 700 students from 10 schools at the baseline to test the effect of the intervention.

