##### Blinding (Masking)

It is not possible for the research team to remain blinded to the group allocation of schools during the study, given the nature of the intervention and the need to manage schools (particularly teachers as they progress through the program). However, the research team were not involved in the *allocation* of schools to the control or intervention groups, as this allocation was conducted externally, thereby removing the possibility of bias in the group allocation. Furthermore, the research team will not be in direct contact with the students or parents during the study (with the exception of students who are absent from school on the day of assessment; a list of absent students will be provided by the school teachers and these students will be contacted through email and invited to complete subsequent follow-up assessments by the research team). As such, no bias is likely to result from the research team’s knowledge of each school’s group allocation.

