#### Statistical Analysis

In this study, primary and secondary outcomes will be analyzed in longitudinal analyses using multilevel mixed-effects regression models. The effects of highest interest are intervention × time interactions that reflect differences between intervention groups in the growth of each outcome over time. The multilevel modeling can account for the expected correlations between different observations of the same individual and between individuals in the same school [55], which would otherwise violate assumptions of independence in traditional regression models. Therefore, models used in these analyses will incorporate both random intercepts and slopes for time at the individual level and random intercepts at the school level. Mixed-effects regression approaches accommodate missing data through the maximum likelihood estimation, an approach that is superior to alternative missing data strategies such as pairwise deletion [56]. Maximum likelihood methods produce unbiased estimates when missing data are assumed to be either missing completely at random or missing at random [57].

Mixed-effects logistic regression with a logit link function will be applied when analyzing binary outcomes. A range of potential fixed effects and random effects structures will be compared using likelihood ratio tests and model fit statistics, such as the Akaike information criterion, to determine the best fitting model for each outcome. For all outcomes, between-condition effect sizes (eg, Cohen *d*) and odds ratios will be calculated along with their corresponding 95% CIs, to provide interpretable estimates of the intervention effects. All analyses will be conducted on an intention-to-treat basis, retaining and analyzing all students and parents in the groups they were originally allocated.

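### The primary model is left to fit-based selection that does not exempt the school-level terms, and the stated model has no school-by-time variation; with 10 to 12 schools this can inflate type I error

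*Protocol article*

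**What the plan says.** All references are to the protocol article.

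- **Statistical Analysis, first paragraph.** Models will include "random intercepts and slopes for time at the individual level and random intercepts at the school level". The target is given as "The effects of highest interest are intervention × time interactions". No school-level random slope for time is listed.
- **Statistical Analysis, second paragraph.** "Mixed-effects logistic regression with a logit link function will be applied when analyzing binary outcomes", which covers both primary outcomes because each is a yes/no item. Then: "A range of potential fixed effects and random effects structures will be compared using likelihood ratio tests and model fit statistics", with AIC named as an example, "to determine the best fitting model for each outcome".
- **Sample Size.** "Five schools, with an average of 70 students per school, are required per intervention group", raised to at least 12 schools in total for school dropout. No intraclass correlation is given.
- **Blinding (Masking).** "It is not possible for the research team to remain blinded to the group allocation of schools during the study". The article does not say who fits the models or when the structure is chosen.
- **Outcomes and Planned Comparisons.** The primary endpoint is 24 months. Comparisons are planned at baseline, 12 months and 24 months.

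**The concern.** The two paragraphs of Statistical Analysis do not fit together. The first fixes a random-effects structure. The second lets the fixed and random structure be decided by fit, outcome by outcome, without saying that the first is a minimum. This is a stated rule, so it is not a detail merely left to a later document.

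Three things are at stake.

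1. **School terms.** Schools are the randomised units, so between-school variance follows from the design. If a fit criterion informed by 10 to 12 units removes it, the arm comparison treats students as independent, which is the violation the article says multilevel modelling is meant to avoid.
2. **School-by-time.** A school random intercept largely cancels out of a contrast of change over time. What limits the precision of an intervention-by-time effect between randomised schools is how much schools differ in their change. The stated model lacks that term, so only the selection step can supply it.
3. **Fixed part.** Whether time is linear or categorical changes what the interaction estimates. Under this rule the choice can depend on the data and differ between the two primary outcomes.

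**Working it through.** **Inputs from the article.** 5 schools per arm with 70 students each: 2 × 5 × 70 = 700 students, as stated. With 15% school dropout, 10 / 0.85 = 11.8, so 12 schools, as stated. Alpha is 0.05, taken as two-sided.

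**The stated size and school variation in change.** The article promises that "this would achieve an 80% power to detect a standardized, between-group mean difference of 0.2". Take times 0, 1, 2, a slope difference of 0.2/2 = 0.1 and no slope variance at either level. Schools per arm are then 2(1 − ρ)(1.96 + 0.842)² / (70 × 2 × 0.1²) = 11.21(1 − ρ), where ρ is the within-student correlation. This rounds up to 5 only for ρ of about 0.55 to 0.64. The article gives no ρ, so the figure can be neither confirmed nor refuted. This formula contains no school variation in change.

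**Assumed.** School ICC of 0.01, 0.02 and 0.05. It applies to one summary per student: an end level (the school intercept) or a change (school-by-time).

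**Method.** J schools of m = 70, no treatment effect, 200,000 simulated trials per setting.

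- Let SSW be the within-school sum of squares and SSB be m times the sum of squared deviations of school means from their arm mean.
- With the school term, the ML estimates are w = SSW / [J(m − 1)] and λ = SSB / J (if λ > w). Without it, s = (SSW + SSB) / (Jm).
- LR = Jm ln s − J(m − 1) ln w − J ln λ. Keep the term if LR > 3.84 (likelihood ratio test) or LR > 2 (AIC).
- The arm difference has variance 4s/(Jm) if the term is dropped and 4λ/(Jm) if kept (z test). The small-sample version uses SSB/(J − 2) with t on J − 2 degrees of freedom.

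**Results, 12 schools (LRT / AIC where two figures).**

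| | ICC 0.01 | ICC 0.02 | ICC 0.05 |
|---|---|---|---|
| Term dropped | 84.1% / 71.2% | 56.8% / 41.2% | 12.4% / 7.0% |
| Type I error after selection, z if kept | 11.5% / 10.3% | 13.3% / 11.5% | 11.6% / 10.8% |
| Type I error after selection, t if kept | 11.2% / 9.6% | 12.1% / 9.5% | 7.4% / 6.2% |
| Always kept, z | 8.3% | 9.6% | 10.4% |
| Always kept, t on 10 df | 5.0% | 5.0% | 5.0% |
| Never included | 13.3% | 20.4% | 35.6% |

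With 10 schools the drop rates are 87% / 76%, 65% / 50% and 20% / 13%, and type I error after selection reaches about 15%.

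**Splitting the sources.** With z throughout, selection adds 11.5 − 8.3 = 3.2 points (LRT) or 10.3 − 8.3 = 2.0 (AIC) at ICC 0.01; 3.7 or 1.9 at 0.02; and 1.2 or 0.4 at 0.05. The step from 5% to 8–10% is large-sample inference with few schools. Leaving the term out altogether is worse than selecting it.

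**Binary check.** Random-intercept logistic model at one time point, 10 schools, 500 trials per cell, assumed prevalence 10% or 30%. At ICC 0.02 the drop rate (LRT / AIC) is 95% / 87% at 10% prevalence and 81% / 66% at 30%. At ICC 0.05 it is 75% / 61% and 39% / 26%. Over ICCs from 0.01 to 0.10, type I error is about 7–15% after selection and 5–10% with the term always kept, with Monte Carlo error of about 1 to 1.6 points.

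**The case against.** **The school intercept is already promised.** One can read selection as working around a fixed core. That reading is possible, but the selection sentence covers random effects without exception, so the text does not secure it.

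**Selection is not the main culprit.** This stands in part. School-by-time is not in the stated model, so selection starting from that model could only add it, and selecting lowers the error compared with never including it. Freezing the stated model and banning selection would therefore make the interaction test worse. The point has to cover the missing term and the reference distribution as well as the selection.

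**The analysis plan will settle it.** Exact model detail is commonly left there, and a plan may exist that is not shown. But the article sets a data-driven rule, and the plan would have to override it.

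**The fixed part is bounded.** The 24-month endpoint and the three planned comparisons narrow the choice, but Statistical Analysis frames the effect as growth over time and leaves the fixed structure open to selection.

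**Stronger readings a reader might infer.**

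- That the model is chosen after unblinding. The documents do not say this. They say the research team knows school allocation and that an external biostatistician oversees the study; the most that follows is that blind selection is not ensured.
- That school terms would be dropped in most trials of this size. That depends on an ICC and prevalence the article does not give. In the Gaussian case with 10 schools it holds only below an ICC of roughly 0.03 (LRT) or 0.02 (AIC).
- That the p-values are invalid. The inflation is conditional; they can be anti-conservative.

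**Conclusion.** The concern holds in limited form. The primary model is not fixed in advance, school-level terms are not protected from fit-based selection, and the term that matters most for intervention by time is absent from the stated model. With 12 schools and assumed ICCs of 0.01 to 0.05, type I error after selection is about 6–13% against a nominal 5%. That excess comes from selection, the missing school-by-time term and large-sample inference together; selection alone accounts for about 0.4 to 3.7 points when z tests are used throughout.

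These figures rest on a Gaussian one-summary-per-student model with equal school sizes, supported by a one-time-point logistic check. The full three-occasion, three-level logistic model was not simulated. The effect of also selecting the fixed part was not quantified; there the argument is that the estimand could change with the data.

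**What to change.** In Statistical Analysis, or in an analysis plan finalised before outcome data are examined by arm:

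1. Prespecify one model for each primary outcome, with the form of time chosen so that the reported contrast is the 24-month effect.
2. Keep school and school-by-time random effects whatever their estimated size or fit.
3. Test the intervention effect with a small-sample method whose degrees of freedom follow the number of schools, and say what is done if a school variance is estimated at zero, so that the test does not fall back to treating students as independent.
4. State an order of simplification for non-convergence that reduces student-level terms first and leaves the school-level terms in place.
5. Move likelihood ratio and AIC comparisons to sensitivity analyses.

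The cost is wording, less modelling flexibility and wider intervals. In the simplified model with 12 schools, moving from a large-sample ML interval to t on 10 degrees of freedom widens it by about (2.23 / 1.96) × √(12/10) = 1.14 × 1.10 = 1.25 times when the estimated school variance is above zero. That also lowers power, so the stated 80% should be rechecked under the final model.

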#### Planned Comparisons

The primary aim of this study is to evaluate the efficacy of the CSP program in comparison with the standard health education received by the control group. Therefore, planned comparisons for each outcome will compare students and parents in the CSP condition with students and parents in the control condition at baseline and 12- and 24-month follow-up.

#### Monitoring

This study will be overseen by an external biostatistician, and any adverse events will be reported to the University of New South Wales Sydney HREC to maintain the integrity of the study including the data collected, trial progress, and ethical compliance. However, given that the intervention reflects normative alcohol and cannabis education provided as part of the PDHPE curriculum, no serious adverse events are anticipated to occur during the study; therefore, a formal steering committee is not required.

### Ethics and Dissemination

#### Research Ethics Approval

Ethics approval was obtained by the University of New South Wales Sydney HREC (HC17852), the Sydney Catholic Education Office (Ref: 201731), and Catholic Education Parramatta (Ref: 060318).

#### Confidentiality

Confidentiality of the collected information will be strictly maintained, and participants’ data will remain anonymous. To access internet-based questionnaires and materials, students and parents will be required to register on the CSP website and once logged in, all data collected will be automatically deidentified, and the database will generate a unique ID code for each participant and the individual’s data files across sessions will be linked with this unique ID code. All data collected will be in a computerized format and stored in password-protected files on university servers, accessible only to the research staff and stored separately to questionnaire data. These procedures mirror those used in previous and existing school-based prevention trials conducted by the research team (eg, The CAP Study, HREC 11274 [50]).

#### Dissemination Policy

The results of this study will be presented to academic peers at conferences and published in health and education peer-reviewed journals. The feedback will be provided to participating schools in the form of a deidentified report of the study’s findings. This report will also be available to students and their parents at the end of the study. When publishing results of this study, no information will be published on the basis of individual cases, and all published data will reflect group data.

## Results

This study is funded by the Australian Government Department of Health from 2016 to 2020 and by Society for Mental Health Research Early Career Research from 2015 to 2017. Enrollment of schools began in January 2018, with 8 out of 12 schools enrolled at the time of submission (enrollment is expected to be complete by October 2018). Baseline assessments are currently underway, and the first results are expected to be submitted for publication in 2019.

## Discussion

### Trialing Climate Schools Plus

This paper describes the design and protocol of the CSP study, the first international trial of an integrated internet-based intervention for students and parents to prevent alcohol and cannabis use. The effectiveness of the CSP program will be assessed through a cluster RCT, relative to health education as usual at 12- and 24-months postbaseline. Contamination will be avoided by the use of a cluster RCT design, in which each school forms its own cluster and is allocated to either the intervention or control group, preventing individuals at the same school being allocated to separate conditions and thus preventing contamination between staff and students at each school. We aim to ascertain whether a combined internet-based approach to drug prevention can be effective in preventing alcohol use among adolescents and improving parents’ self-efficacy to prevent their children from using substances.

### Strengths and Limitations

To date, approaches to substance use prevention have traditionally focused on adolescents themselves, despite evidence suggesting that parents play a critical role in substance use initiation [10-13]. The CSP study addresses the need for an integrated program for both students and their parents that is potentially sustainable through internet-based facilitation. The CSP program is built on a decade of sound research, which has shown that the internet-based *Climate Schools* programs for students are effective in preventing substance use. The expansion of this model to involve parents has the potential to improve prevention effects and provides a sustainable and scalable model for both students and parents.

The CSP program utilizes cartoon storylines to engage students and maintain their interest and internet-based technology to engage parents and improve ease of access to substance use prevention information, based on a successful evidence-based intervention [32,33]. Importantly, the internet-based nature of the CSP parent program (namely the on-demand webinars, modules, and parent summaries), provides parents with the flexibility to access the program material remotely at a time and location of their choice, which has the potential to improve the uptake of the program. Nonetheless, engagement and adherence are common challenges faced in trials of internet-based interventions [58,59]; therefore, this study uses a number of strategies to increase parent engagement (including frequent email communication, an “Invite Your Parent” icon displayed on students’ homepage, facilitation of a parent-generated “shared” set of school-specific rules among parents, etc). All of these engagement strategies are sustainable if the program were to be delivered outside of a trial setting. Importantly, the detailed measurement of internet-based engagement and interaction with the program will provide important information about the feasibility of engaging parents in internet-based substance use prevention trials in the future.

A potential limitation of this study is the use of self-report, which could be subject to the social desirability bias. However, previous research has demonstrated that self-report measures of substance use among adolescents have yielded excellent discriminant [50] and predictive [51] validity [46,52] and have been found to be a reliable method of assessing the frequency and quantity of adolescent alcohol use [53]. In addition, researchers will use strategies to maximize the accuracy of self-report, which have been successful in previous school-based trials [18-21,23,24,37,46]; these strategies include blind administration of any assessments within schools and a strong emphasis on anonymity and confidentiality.

Attrition is another potential limitation to this study, which could result from students not being present on the day of assessments or not providing correct or complete contact details to allow the research team to link their responses over time. However, missing data are likely to be at random, and the chosen data analytic techniques (mixed-effects regression modeling) use all available data, thus reducing the bias brought about by participant attrition.

The school sample used in this study (ie, Independent and Catholic school types) may limit the generalizability of the findings to the broader population. However, we do not expect this factor to markedly impact the outcomes of the trial, as previous research has found that the consumption and frequency of cannabis use within independent (nongovernment) schools was comparable to the larger population of young people of the same age [18,60], suggesting that the consumption and frequency of substance use is comparable between government and nongovernment school types. Furthermore, the research team aimed to recruit a range of schools from various geographic regions for the study and used a stratified randomization scheme when allocating schools to conditions to improve the generalizability of the findings.

An additional limitation of this study involves the need to obtain active consent from participants, as this might introduce selection bias. We aim to overcome this risk of selection bias with a robust study design. As this is an RCT, both participants in the intervention condition and control condition will volunteer to participate; therefore, the impact of volunteering is likely to be spread evenly across the two conditions. Although active or voluntary consent procedures can introduce selection bias [61], previous studies have found no differences in alcohol or illicit drug use among students with passive or active consent [62]. Moreover, we aim to minimize the chance of selection bias by offering support for participants, to ensure their understanding of the consent form and what is required if they participate in the study (ie, consent forms will be offered in both electronic and hard-copy forms, and if required, the form can be translated into the preferred language of the participants). Ideally, passive consent procedures would be used to maximize the number of participants taking part in the trial; however, ethical restrictions meant that we were required to use active consent procedures in this study. As such, future research would benefit from the use of passive consent procedures to reduce the impact of selection bias on the outcomes in the study.

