## Methods

### Participants, Interventions, and Outcomes

#### Participants

##### Study Setting and Recruitment

This study is set in Independent and Catholic secondary schools in Australia. We obtained Human Research Ethics Committee (HREC) approval to approach Independent schools (HREC 17852) and Catholic schools in two dioceses in the Greater Sydney area (reference: 201731 and 060318) and invite them to participate. In October 2017, 156 schools were approached using a variety of methods, including advertisement during the Personal Development Health and Physical Education (PDHPE) Teachers’ Association Annual Conference, emails sent directly to schools or school principals, newsletter entries (ie, the Independent Secondary Schools Association and *Climate Schools* newsletters), posts on social media, and through follow-up phone calls. Parents will first be recruited to participate in the CSP study when their students bring home the parent permission form, along with a postcard containing information about the study and instructions on how to register. Then, they will also be recruited through an email sent from their school with information about the study, a link to a short, 45-second video introducing the aims of the study and instructions on how to register; this involves parents consenting for their adolescent’s and their own participation. Next, to access the content of the program, parents will need to register for an account through the CSP website. Students who have received parental permission to participate in the study will be approached to register and consent during their regular PDHPE classes and will be given the opportunity to send an email to their parents, reminding them to register for the program through an “Invite Your Parent” icon on the CSP website.

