##### Consent or Assent

After school principals agree to participate in the study, active consent will be sought individually from parents, students, and teachers. Parents will be asked to provide active consent for (1) their child’s participation in the study and (2) their own participation. Eligible students with parental consent will be directed to the participant information statement and consent form when registering on the CSP website, and all parents will similarly be directed to their participant information statements and consent forms when registering for the first time. Conversely, students and parents in the CSP group who do not consent to participate in the research trial will still be offered access to the content of the program; however, they will not be prompted to complete assessment surveys, and no data will be collected from those individuals.

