#### Participant Timeline

Students and parents in the CSP group will be invited to register for the CSP program online during the first year of the study (for the majority of schools, this will be during term 1 of 2018; however, for some, it will be term 2 or 3 of 2018). Students will complete their registration and baseline survey during their regularly scheduled PDHPE classes, and their teachers will facilitate their progression through the *Climate Schools: Alcohol* lessons. During the first week of the intervention, parents register for the program and are invited to view the webinar, participate in the interactive rule-ranking component, and explore the available modules. Approximately 8 weeks after registering for the program, parents and students will be prompted to complete an evaluation of the program content online, through the CSP website. Similarly, in 2019, students will complete the 12-month follow-up questionnaire, and their teacher will facilitate their progression through the lessons. Simultaneously, parents of these students will be invited to view the second webinar, the second round of rule-ranking, and invited to explore year 9 parent modules. Students and parents will also be asked to complete an evaluation of the year 9 program through the CSP website, as they did in the previous year. Finally, in 2020, parents and students will be asked to complete the 24-month follow-up questionnaire; a reminder email will be sent to nonresponding parents and students 1 week after they are invited to complete it and another reminder 1 week later. Table 1 summarizes the student and parent involvement in the study.

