#### Assignment of Interventions

##### Allocation

Following school consent, schools have been randomly allocated to the CSP or control group by an external researcher; this process involved stratified random allocation, in which schools were divided into three mutually exclusive strata: (1) coeducational (mixed males and females) school, (2) single-sex or predominantly girls school, and (3) single-sex or predominantly boys school. The allocation was random within strata to achieve balance across intervention and control groups with respect to the number of males and females participating in the trial. Randomization was achieved using a randomization table created in StataSE, version 14, using the Stratarand procedure. The randomization sequence was computer-generated by an external biostatistician, who then informed the research team of which group each school had been allocated to.

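### Families are recruited after their school is allocated, so the assurance that volunteering is evenly spread between arms is unsupported and differential consent can bias the comparison

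*Protocol article*

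**What the plan says.** On the order of events, the Allocation section states: "Following school consent, schools have been randomly allocated to the CSP or control group by an external researcher". Consent or Assent states: "After school principals agree to participate in the study, active consent will be sought individually from parents, students, and teachers". Study Setting and Recruitment describes the approach to families as still to come and made through the school: "Parents will first be recruited to participate in the CSP study when their students bring home the parent permission form".

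On what families know when they are approached, Participant Timeline states: "Students and parents in the CSP group will be invited to register for the CSP program online during the first year of the study", and then: "During the first week of the intervention, parents register for the program". Consent or Assent adds that "students and parents in the CSP group who do not consent to participate in the research trial will still be offered access" to the program content, and that no data are collected from people who decline.

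On the consequence, Strengths and Limitations names active consent as a possible source of selection bias. It answers that this is a randomized trial with volunteers in both arms, so that "the impact of volunteering is likely to be spread evenly across the two conditions".

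Two other passages bear on the point. The Control Group section says that the registration and consent process is the same in both arms. Statistical Analysis specifies intention-to-treat, with intervention by time interactions as the effects of main interest.

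**The concern.** Randomizing schools balances the year groups, in expectation. It balances the people who volunteer from those year groups only if they decide before allocation or without knowing it. Once the arm is known, the decision to consent can depend on it.

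The two arms offer different things. CSP families are offered webinars, modules and lesson summaries together with the surveys; control families are offered surveys alongside usual health education. If the families who consent in one arm differ in drinking risk from those who consent in the other, the arms differ before any intervention effect.

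At stake is the comparison on both primary outcomes. The intention-to-treat set consists of consenters. Because nothing is collected from decliners, the trial data alone cannot show whether selection differed by arm. The planned effect is small (standardized difference 0.2), so a modest difference in selection could be a noticeable fraction of it.

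**Working it through.** **Step 1: order of events.** Set side by side, the sections give this sequence: the school consents; the school is allocated (past tense in Allocation); parents and students are approached and consented through the school (future tense in Study Setting and Recruitment and in Consent or Assent). In Participant Timeline, families already belong to the CSP group when they are invited, the invitation is to the program, and parents register in the first week of the intervention. At least in the CSP arm, then, consent follows allocation and the invitation reveals the arm. The Blinding section says that the research team is not blinded. No section says that families or recruiting school staff are unaware of the arm at consent.

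**Step 2: does the stated inference follow?** Volunteers in both arms are not enough; the volunteering process must also be independent of arm. The article supports this only by noting that the trial is randomized. Its other argument, that studies found similar substance use under active and passive consent, compares consent methods and says nothing about differences between arms.

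**Step 3: illustration of size.** The plan gives no consent rate or drinking prevalence, so these inputs are assumptions:
- no true effect; 25% of each year group drink by 24 months
- control: consent unrelated to future drinking, so prevalence among consenters is 25%
- CSP: future drinkers' families have consent odds k times those of other families, with k = 0.8, 0.7 or 0.5
- overall CSP consent C of 70%, 90% or 95%
- raw comparison at 24 months

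Let c0 be CSP consent among other families and c1 consent among future drinkers' families. Solve

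0.25·c1 + 0.75·c0 = C, with c1/(1 − c1) = k·c0/(1 − c0).

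Prevalence among CSP consenters is 0.25·c1/C. The spurious odds ratio against control is c1/c0.

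The plan's effect of d = 0.2 is put on the odds ratio scale by ln OR = d·π/√3 = 0.2 × 1.814 = 0.363, so OR = exp(−0.363) ≈ 0.70. The share of the planned effect is −ln(spurious OR)/0.363.

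| C | k | c1 | c0 | CSP prevalence | Spurious OR | Share of planned effect |
|---|---|---|---|---|---|---|
| 70% | 0.8 | 66.4% | 71.2% | 23.7% | 0.93 | 19% |
| 70% | 0.7 | 64.2% | 71.9% | 22.9% | 0.89 | 31% |
| 70% | 0.5 | 58.5% | 73.8% | 20.9% | 0.79 | 64% |
| 90% | 0.8 | 88.4% | 90.5% | 24.6% | 0.98 | 6% |
| 90% | 0.7 | 87.4% | 90.9% | 24.3% | 0.96 | 11% |
| 90% | 0.5 | 84.8% | 91.7% | 23.5% | 0.92 | 22% |
| 95% | 0.8 to 0.5 | 94.2% to 92.2% | 95.3% to 95.9% | 24.8% to 24.3% | 0.99 to 0.96 | 3% to 11% |

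With k = 1 the spurious OR is 1. With k above 1 it exceeds 1 and would mask a benefit. The table shows one direction only.

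**Step 4: what the planned model does.** With baseline outcomes measured and intervention by time as the target, a difference between arms that is already present at baseline is partly absorbed. A difference in how fast drinking starts is not, because that growth is what the interaction estimates. The Introduction places the program before marked exposure to alcohol, so baseline drinking is likely to be a weak marker of who starts by 24 months.

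**The case against.** The strongest case on the other side has four parts.

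- **The article is cautious.** It says only that an even spread is likely, and it lists active consent as a limitation. That is fair, but the reason it gives for the likelihood is the randomized design, and the order of recruitment removes that reason.
- **The arms are handled alike.** The consent process is the same in both. CSP families can have the program without joining the research, so access is no inducement to consent. This stands as mitigation and is one reason the direction cannot be predicted. It equalizes the procedure, but it does not equalize what is offered or conceal the arm.
- **The analysis uses baseline.** This also stands in part: the raw 24-month comparison in the illustration is not the planned analysis and does not estimate its bias. Differences in growth remain.
- **Participation may be nearly complete.** Sample Size assumes that most, if not all, of the year group take part. If so, the bias is small, as the 95% row shows. The article's own discussion of active consent means that this cannot be taken for granted.

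A reader might infer that selection bias has occurred, or that the sentence on volunteering is shown to be false. The documents support neither. They show a route, with no evidence on its occurrence, size or direction, and the trial flow in Figure 1 is not shown. A reader might also take the 64% figure as the expected bias; it needs both the lowest consent odds ratio and 70% consent.

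**Conclusion.** The concern holds in this form: individual consent follows school allocation, the invitation reveals the arm at least for CSP families, and the claim of even volunteering is therefore unsupported. Differential consent can bias the primary comparison in either direction. Intention-to-treat among consenters does not correct this, and the intervention by time model corrects it only in part.

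On the stated assumptions the spurious odds ratio runs from 0.93 to 0.79 at 70% consent and from 0.98 to 0.92 at 90%, against a planned value of about 0.70, and it approaches 1 as consent nears completeness. These figures show what could happen in a raw 24-month comparison and do not estimate bias in this trial. The conclusion about the order of events rests on the text alone.

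**What to change.** 1. In any school not yet allocated or not yet recruiting families, complete parent and student consent and the baseline survey, with identical recruitment text, before the allocation is released to the school. The Results section reports recruitment "with 8 out of 12 schools enrolled at the time of submission", so this could apply to up to 12 − 8 = 4 schools if all eight had started. The article does not say which schools had been allocated or had begun recruiting families, so the number is an inference.
2. Record the recruitment sequence used by each school.
3. For all schools, report consenters as a share of year 8 enrolment by arm, and compare the baseline characteristics of consenters between arms. The baseline measures are already planned; only the enrolment denominators are new.
4. Replace the sentence on even volunteering with a statement that recruitment after allocation leaves a residual risk of differential selection between arms.

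The first item costs a short delay in scheduling lessons and leaves two recruitment sequences within one trial, hence the second item. The others cost a few lines of text and an enrolment count from each school. None removes the risk in schools where families have already been recruited with the arm known; there it can only be described.
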